**Primary outcomes: safety**						
	Monitoring of hyperthermia (body temperature of ≥38°C) or hypothermia (body temperature of ≤36°C)	✓	✓	✓	✓	
	Oxygen saturation of <90% for >15 seconds	✓	✓	✓	✓	
	Heart rate of >160 beats/minute during inactivity or <80 beats/minute for >15 seconds	✓	✓	✓	✓	
	Allergic contact reaction of grade ≥3 (Ring and Messmer classification [14])	✓	✓	✓	✓	
**Secondary outcomes**						
	Description of the number of neonates presenting each adverse event individually (skin lesion, dehydration, diarrhea, etc)	✓	✓	✓	✓	
	Monitoring of serum bilirubin levels	✓				✓
	Monitoring of transcutaneous bilirubin levels	✓				✓
	Evolution of the EDIN^a^ score: neonatal pain and discomfort scale	✓			✓	
	Number of feedings, number of diaper changes and the causes of cessation of phototherapy			✓	✓	
	Perceptions of the parents with the use of the device and interaction with their child					✓

^a^EDIN: Échelle de Douleur et d'Inconfort du Nouveau-né.

### Sample Size

This is a pilot feasibility study. The number of subjects is therefore not calculated on the basis of statistical assumptions. We propose to include 10-15 neonates and their parents in order to obtain evaluable data from 10 parent-neonate pairs. The feasibility objective is to obtain a minimum proportion of 90% (ie, 9 of 10) of the neonates included in this study, having undergone PT without unacceptable and unexpected toxicities.

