**Methods:**

This interventional, exploratory, simple group, nonrandomized, single-center trial will be conducted at Lille Hospital. In total, 10-15 neonates and their parents will be included to obtain evaluable data from 10 parent-neonate pairs. Neonates weighing more than 2500 g at birth and born with ≥37 weeks of amenorrhea that required PT in accordance with the guidelines of the National Institute For Health and Clinical Excellence will receive one 4-hour session of illumination. Total serum bilirubin and transcutaneous bilirubin levels were obtained at the start and 2 hours after the end of PT. Cutaneous and rectal temperatures, heart rate, and oxygen saturation will be measured at the beginning and during PT. The number of subjects is therefore not calculated on the basis of statistical assumptions. We aim to obtain a minimum proportion of 90% (ie, 9 of 10) of the neonates included, who have been able to undergo 4-hour PT without unacceptable and unexpected toxicities. We will calculate the mean, median, quartiles, minimum and maximum values of the quantitative parameters, and the frequency of the qualitative parameters. The rate of patients with no unacceptable and unexpected toxicities (ie, the primary endpoint) will be calculated.

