## Methods

### Trial Design

This interventional, exploratory, simple group, nonrandomized, single-center study will include 10-15 neonates in order to obtain evaluable data from 10 parent-child pairs.

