### Study Objectives and Outcomes

The primary objective of the study is to evaluate the safety of the BUBOLight PT device as an alternative to conventional tunnel PT under the usual conditions for the management of jaundice in neonates.

Safety will be based on the proportion of neonates who received complete and effective 4-hour PT with the BUBOlight device and did not experience unacceptable and unexpected toxicities (target set at least 90% of neonates).

The key secondary objectives are the individually frequency of each adverse effect, monitoring of serum bilirubin and transcutaneous levels under phototherapy, and the perceptions of parents and health team with the use of the device (comfort, heat, humidity, ease of breastfeeding, proximity, and possibility of contact with the baby) and causes of PT discontinuation. Table 1 summarizes the study objectives and outcomes.

**Table 1 table1:** Study objectives and outcomes.

Outcomes		Inclusion: initiation of phototherapy (hour 0)	1 hour after the beginning of phototherapy	2 hours after the beginning of phototherapy	4-hour effective phototherapy	2 hours after the end of phototherapy

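### The 90% target counts 9 of 10 neonates but is set on all neonates included, of whom there may be 10 to 15; the two agree only at exactly 10

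*Protocol article*

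**What the plan says.** Three places in the protocol article give the enrolment range. The Sample Size section says "We propose to include 10-15 neonates and their parents in order to obtain evaluable data from 10 parent-neonate pairs". Trial Design says the study "will include 10-15 neonates in order to obtain evaluable data from 10 parent-child pairs". The Methods paragraph of the Abstract says "In total, 10-15 neonates and their parents will be included to obtain evaluable data from 10 parent-neonate pairs".

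The target stands next to the range in the Sample Size section: "The feasibility objective is to obtain a minimum proportion of 90% (ie, 9 of 10) of the neonates included in this study". The Abstract uses the same denominator and the same count of 9 in 10.

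Study Objectives and Outcomes defines success in two parts. The first is completion: "Safety will be based on the proportion of neonates who received complete and effective 4-hour PT with the BUBOlight device". The second is that the neonate "did not experience unacceptable and unexpected toxicities (target set at least 90% of neonates".

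The Statistical Analysis section then describes the primary endpoint only as the rate of patients free of such toxicities. It names no denominator and does not repeat the completion requirement. The article does not say what makes a pair evaluable.

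**The concern.** The target has two denominators. One is the neonates included, who may number 10 to 15. The other is the 10 implied by the count of 9 in 10, which matches the planned number of evaluable pairs. They coincide only if nobody beyond the tenth neonate is included, and the plan expressly allows more.

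The choice matters because of how success is defined. A neonate whose session is cut short has not met the endpoint. The same neonate is also an obvious candidate to be called non-evaluable. Evaluability is set for the pair, and Table 1 places the parents' perceptions and the second bilirubin measurements 2 hours after phototherapy ends, whereas the safety items are recorded from the start to hour 4. A neonate with usable safety data could therefore be lost because a later item is missing. If such neonates leave the denominator and others take their place, the primary rate is calculated on a group partly selected for having succeeded. The article also states that the analysis is unblinded, so evaluability could be judged with the outcome known.

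At stake is whether the study's only numeric target can be called met, and what a reader of the reported rate takes it to mean.

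**Working it through.** **Inputs from the protocol article.** Included: N = 10 to 15. Evaluable pairs: 10. Target: at least 90%, given as 9 of 10. Success: 4-hour session completed and no unacceptable and unexpected toxicity. There is no sample-size formula to reproduce; the article says the number is not based on statistical assumptions.

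**Step 1. The plan's own figure.** 9/10 = 0.90. It reproduces, for N = 10.

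**Step 2. The same count over the allowed range.** Nine successes divided by N, and the successes that 90% of N requires, which is 0.9 × N rounded up:

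| N included | 9/N | Successes needed for 90% | Failures allowed |
|---|---|---|---|
| 10 | 90.0% | 9 | 1 |
| 11 | 81.8% | 10 | 1 |
| 12 | 75.0% | 11 | 1 |
| 13 | 69.2% | 12 | 1 |
| 14 | 64.3% | 13 | 1 |
| 15 | 60.0% | 14 | 1 |

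At N = 15 the two readings require 9 or 14 successes.

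**Step 3. The extreme case the wording allows.** Fifteen are included and started, five do not complete and are treated as non-evaluable, and one of the other ten fails. Reported on evaluable pairs: 9/10 = 90%. On all included: 9/15 = 60%, exact (Clopper-Pearson) 95% CI 32.3% to 83.7%. If all ten evaluable neonates succeed, 100% is reported against 10/15 = 66.7%.

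**Step 4. Chance of meeting the target under each reading.** The documents give no rates, so these are assumptions: each started neonate stops early with probability d, independently, and 5% of completers have a qualifying toxicity. Success per started neonate is p = (1 − d) × 0.95.

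*With replacement up to 15.* Two things must happen: at least 10 completers among 15, and at most one toxicity among the ten. The second has probability 0.95^10 + 10 × 0.05 × 0.95^9 = 0.5987 + 0.3151 = 0.914.

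*Ten neonates counted as started.* The probability is p^10 + 10 × p^9 × (1 − p).

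| d | p | P(at least 10 completers of 15) | Met, with replacement | Met, 10 as started |
|---|---|---|---|---|
| 20% | 0.76 | 0.939 | 0.939 × 0.914 = 0.858 | 0.0643 + 0.2030 = 0.267 |
| 10% | 0.855 | 0.998 | 0.998 × 0.914 = 0.912 | 0.2088 + 0.3540 = 0.563 |
| 5% | 0.9025 | >0.999 | 0.914 | 0.3585 + 0.3873 = 0.746 |
| 0% | 0.95 | 1 | 0.914 | 0.914 |

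The gap is 59 percentage points at 20% stopping, 35 at 10%, 17 at 5%, and nil if nobody stops early.

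**Step 5. How likely the extreme case is.** Under the same assumptions, the probability that enrolment runs to exactly 15 and the ten completers contain exactly one toxicity is C(14,5) × d^5 × (1 − d)^10 × 10 × 0.05 × 0.95^9. With C(14,5) = 2002 this is 0.0688 × 0.3151 = 2.2% at d = 20%, and 0.0070 × 0.3151 = 0.2% at d = 10%.

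**The case against.** The strongest reply is that the article never says non-completers are replaced. It names the included neonates as the denominator and puts completion inside the endpoint, so on its face a neonate who stops early counts as a failure, and 9 in 10 merely illustrates 90% at the smallest enrolment. A reader might infer that the sponsor plans to drop failures, or that the primary rate is biased. The text supports neither as a statement of fact. It only leaves that route open.

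Second, concealment would be hard. Causes of stopping phototherapy are a listed secondary outcome, data on discontinuation are collected, and the Statistical Analysis section promises individual description of all data. With at most 15 infants, five lost sessions should be visible. This stands, and limits the harm. It does not settle which rate is the primary result.

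Third, this is a descriptive pilot reported in a condensed article, and the full protocol may define evaluability. That is fair, and neither the missing definition nor the missing sample-size calculation is criticised here. But defining evaluable would not reconcile 90% of those included with 9 of 10 when up to 15 may be included. That conflict is in the text shown.

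Fourth, stopping rates of 10% to 20% in a single 4-hour inpatient session have no support in the documents. This is correct, which is why lower rates are also shown.

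**Conclusion.** The point holds as an inconsistency in the primary target: it is wrong as written and should be fixed. The stated count and the stated denominator disagree at every enrolment from 11 to 15, and the count alone could be met with anything from 90% down to 60% of included neonates succeeding.

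It would be tempting to say that a true 60% success rate can be passed off as 90%. The documents do not support this. The 60% is an observed proportion in the most extreme configuration, with a probability of about 2% or less under the rates assumed here. The more useful measure is the chance of meeting the target: about 86% against 27% at an assumed 20% stopping, and 91% against 56% at 10%. These figures rest on independence, 5% toxicity among completers, and replacement of every non-completer up to 15. The difference vanishes as early stopping approaches zero.

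The severity stays at should-fix. The analysis is purely descriptive and no formal go/no-go rule depends on the target; the Discussion only expresses the hope of a comparative study after positive results.

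**What to change.** Make the same change in the Abstract (Methods), Trial Design, Study Objectives and Outcomes, Sample Size, and Statistical Analysis:

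- Define the primary denominator as every neonate in whom phototherapy with the device is started. Report separately any neonate included but never started; only these may be replaced for the primary endpoint.
- Count non-completion of the effective 4-hour session as not meeting the endpoint, as the objectives section already implies, and report the reason for each stop. The short interruptions that the Intervention section already allows are not non-completion. Counting stops unrelated to the device as failures is a choice, so the reasons let a reader separate them.
- Restate the target as at least 90% of started neonates, meaning at most one failure for any number from 10 to 15 (9/10, 10/11, 11/12, 12/13, 13/14 or 14/15).
- In Statistical Analysis, give the primary rate with this denominator and with the completion component.
- Keep evaluable pairs for the questionnaire and bilirubin summaries only.

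The cost is wording. No extra neonates or procedures are needed. The reported rate may be less favourable, and the target becomes harder to meet if any sessions stop early.

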### Allocation and Randomization

There will be no randomization in this study; all neonates will receive PT with the BUBOLight device.

### Implementation and Blinding

The study will not involve blinding as it is an uncontrolled clinical trial with a single group of patients receiving the same treatment. Data will also be analyzed without blinding.

### Intervention

Neonates who have not been discharged from the hospital and who require PT for jaundice will be included in the study after verification of the inclusion and exclusion criteria.

As shown in Figure 3, parent-neonate pairs who meet all of the inclusion criteria and none of the exclusion criteria are invited to participate in the study, which will involve a single visit.

The study will include an effective 4-hour PT session (which may be discontinued for a few minutes to change diapers if necessary) followed by a 2-hour rest period in accordance with the recommendations of the French National Reference Center for Perinatal Hemobiology. Serum bilirubin levels will be determined upon initiation of PT (H0) and 2 hours after the effective end of PT; that is, at approximately H0+6 hours, in order to check for a reduction in bilirubin levels. Transcutaneous measurement with a bilirubinometer (Dräger Jaundice Meter JM-105) will be also performed upon initiation of PT and 2 hours after the effective end of PT.

Heart rate and oxygen saturation will be continuously recorded using a monitor, which is usually used during PT. Alarms will be set to detect desaturation and bradycardia episodes lasting >15 seconds. The investigator will check the scope at the end of the monitoring period for false episodes related to an artefact.

In addition, axillary and cutaneous temperatures will be regularly monitored in order to prevent any risk of dehydration and hyperthermia. Room temperature will also be measured.

The neonatal pain and discomfort scale (Échelle de Douleur et d'Inconfort du Nouveau-né [EDIN] score) and the opinion of parents and health professionals on the use of the device will also be sought.

**Figure 3 figure3:**
[figure not shown]
Study design and data collection.

### Variables and Data Collection

The collected medical data will consist of demographic and medical data (sex, weight, height, day of birth, and gestational age), risk factors for severe hyperbilirubinemia, and the blood type of the mother and the child.

To achieve the primary and secondary endpoints, we will measure serum and transcutaneous bilirubin levels.

Temperature, oxygen saturation, and heart rate data will be monitored throughout the PT session. EDIN scores of 0-15 will be considered for monitoring neonatal pain and discomfort, and data regarding PT discontinuation will be collected (including the number of changes, feedings, and cares).

Parents and medical staff will be asked to complete feedback questionnaires at the end of the observation period. Data will be collected on device usability, assessment of noise, and the design of the device.

### Data Management

This study complies with methodology MR-001 of the Commission nationale de l'informatique et des libertés for the treatment of personal data, which is a simplified declaration of data from medical research to the French National Data Protection Authority. The only persons authorized to access data and modify the files generated in this study are those who are directly involved in the study. These participants will have access to data and be able to modify them at any moment in consultation with one of the referring investigators of the study. The sponsor affirms the patient’s right to protection against invasion of privacy.

The data will be collected through a case report form and be saved in an electronic file (database). All participants will receive a trial identifier, and only the investigator knows the personal details. The sponsor’s monitor will plan several monitoring visits, after initial enrollment at the study site and periodically to assess data quality and study integrity. The sponsor’s monitor will review the study records and directly compare them with the source documents, discuss the conduct of the study with the investigator, and verify that the facilities remain acceptable. The trial will be monitored in accordance with the monitoring plan. A planning meeting with the principal investigator will hence be held before the start of the trial. During the trial, several checkpoints are defined, including the presence of signed informed consent forms obtained by the investigator, adherence to the inclusion and exclusion criteria, reporting of any adverse events, and the monitoring of all steps of patient follow-up. At the end of the trial and once the final analysis is completed and validated, all the files are sealed and archived in accordance with specific procedures at a secure location at the clinical research department of the sponsor.

The trial support unit will coordinate the data management. The database is stored and secured on the network of Lille University Hospital. Before the closeout of the database, data monitoring will be performed using XLSTAT software (Addinsoft Inc) in accordance with consistency guidelines set with the project manager (eg, missing data, outliers, and inconsistency among several variables). The data will be analyzed at the OncoTHAI Laser Assisted Therapies and Immunotherapies for Oncology unit (U1189, Inserm, CHU Lille). Only the investigator participating in the study or a collaborator designated by the physician and participating in the study may modify the data. The study data will be archived for a minimum period of 15 years from the end of the study or its early termination without bias toward the laws and regulations in force.

### Statistical Analysis

Security and acceptability will be assessed using descriptive data. All data will be described individually and summarized using the following statistical parameters:

*Primary objective:* the mean, median, quartiles, minimum and maximum values of the quantitative parameters, and the frequency of the qualitative parameters will be calculated. The rate of patients with no unacceptable and unexpected toxicities (primary endpoint) will be calculated.

*Secondary objectives:* bilirubin levels and EDIN score data for neonatal pain and discomfort will be expressed as means, medians, quartiles, and minimum and maximum values at each measurement time.

Changes in serum and transcutaneous bilirubin levels among PT initiation (H0), H0+4 hours (only transcutaneous), and 2 hours after the end of PT, and changes in the EDIN score between PT initiation (H0) and after 4 hours of actual treatment will also be described. Furthermore, we will calculate the mean, median, quartiles, minimum and maximum values of the quantitative parameters (number of feedings, diaper changes, and care), and the frequency of the qualitative parameters (perceptions of the parents and the health team regarding the use of the device and interaction with their infant).

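### The objectives require a completed 4-hour session for primary success, but the analysis section counts only freedom from toxicity, and no rule classifies a toxicity-free session that ends early

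*Protocol article*

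**What the plan says.** The protocol article describes its primary measure in five places.

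- **Study Objectives and Outcomes:** the measure is "the proportion of neonates who received complete and effective 4-hour PT with the BUBOlight device and did not experience unacceptable and unexpected toxicities". Success has two parts, completion and freedom from toxicity, and the goal is 90% or more.
- **Abstract, Methods (target):** the 90% refers to neonates "who have been able to undergo 4-hour PT without unacceptable and unexpected toxicities". Both parts are present.
- **Abstract, Methods (last sentence):** "The rate of patients with no unacceptable and unexpected toxicities (ie, the primary endpoint) will be calculated". Only the toxicity part remains.
- **Sample Size:** the 90% (9 of 10) refers to neonates "having undergone PT without unacceptable and unexpected toxicities". Neither completeness nor the 4-hour length is mentioned.
- **Statistical Analysis:** "The rate of patients with no unacceptable and unexpected toxicities (primary endpoint) will be calculated". Only the toxicity part remains.

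The primary block of Table 1 lists temperature, oxygen saturation, heart rate and allergic contact reaction. It has no item for completing the session. Causes of stopping phototherapy (PT) are a secondary outcome.

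**The concern.** The 90% target is the only success threshold in the study, and the text attaches it to two different quantities. An analyst working from the objectives would count neonates who completed the session without toxicity. One working from the analysis section and the primary block of Table 1 would count neonates without toxicity, whether or not they completed.

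The two counts differ for one group: neonates whose session ends early for a reason that is not a primary toxicity, such as a device fault or a parent's request. No section says how to classify them. A session stopped for a primary toxicity fails under both definitions, and the short diaper-change pauses allowed under Intervention are not early stops.

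The title and the Sample Size section present this as a feasibility study. Whether the full session can be delivered is central to that question, and a toxicity-only rate does not measure it.

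**Working it through.** **Inputs from the protocol.** Target 90%, given as 9 of 10 (Sample Size). Between 10 and 15 neonates are included to obtain 10 evaluable pairs; the article does not define evaluable. It gives no early-stopping or toxicity rate, so the counts and rates below are assumptions.

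**The plan's own figure.** 0.90 × 10 = 9, so 9 of 10 reproduces.

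**Case A: early stops stay in the denominator.** Let n = 10, t = neonates with a primary toxicity, and s = neonates stopped early without one.

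- Analysis section: (n − t)/n
- Objectives: (n − t − s)/n
- Difference: s/n, never negative when n is the same for both

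With t = 0:

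| s | Analysis section | Objectives | Target under objectives |
|---|---|---|---|
| 0 | 10/10 = 100% | 10/10 = 100% | met |
| 1 | 10/10 = 100% | 9/10 = 90% | met |
| 2 | 10/10 = 100% | 8/10 = 80% | missed |
| 3 | 10/10 = 100% | 7/10 = 70% | missed |

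Two early stops therefore reverse the conclusion. With t = 1, a single further early stop is enough: (10 − 1)/10 = 90% is met, and (10 − 1 − 1)/10 = 80% is missed.

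**Case B: early stops are called non-evaluable and replaced.** Assume no toxicity and 10 clean completers.

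- 12 started, 2 stopped early: 10/12 = 83% of all who started, against 10/10 = 100% of completers.
- 15 started, 5 stopped early: 10/15 = 67%, against 10/10 = 100%.

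Replacement hides the early stops even if the objective's definition is used.

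**Chance of meeting the target (illustration).** For X ~ Binomial(10, p), P(X ≥ 9) = 10p⁹(1 − p) + p¹⁰. The toxicity-only definition uses p = P(no toxicity). The two-part definition uses p = P(no toxicity) × P(complete), assuming independence.

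| P(no toxicity) | Toxicity only | Two-part, 95% complete | 90% complete | 80% complete |
|---|---|---|---|---|
| 0.90 | 0.736 | 0.563 | 0.407 | 0.183 |
| 0.95 | 0.914 | 0.746 | 0.563 | 0.267 |
| 0.98 | 0.984 | 0.852 | 0.666 | 0.329 |

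For example, 95% toxicity-free and 90% complete gives p = 0.95 × 0.90 = 0.855 and a probability of 0.563, against 0.914 on toxicity alone.

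**The case against.** The strongest reply is that the analysis sentence is shorthand for the endpoint already defined in the objectives. The Abstract supports this: it gives the full target and soon afterwards uses the short form, as if the two were the same. The article also condenses a fuller protocol. All data are to be described individually, and causes of stopping are collected, so in about ten neonates an early stop would probably be visible.

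Part of this stands. A reader might infer that the protocol has decided to count an aborted session as a success. It has not; it is silent on the classification, and the success follows only from a literal reading. Nor would the feasibility information be lost, since it is planned as secondary data.

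The shorthand reading does not settle the matter, however. The Sample Size section, the primary block of Table 1 and the Statistical Analysis section all leave out 4-hour completion, and two sentences label the toxicity-free rate itself as the primary endpoint. This is a contradiction in the printed text, not a detail left to another document.

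A second tempting reading comes from Variables and Data Collection: "To achieve the primary and secondary endpoints, we will measure serum and transcutaneous bilirubin levels". A reader might infer that *effective* PT in the objectives means PT that lowers bilirubin. The document does not support that. Intervention uses the word for delivered time, allowing brief pauses; Statistical Analysis refers to actual treatment time; and Table 1 lists bilirubin only as secondary. The sentence is loose, but it does not redefine the endpoint.

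**Conclusion.** The point holds as an inconsistency in the definition of the primary endpoint that can change whether the target is met. With 10 neonates in the denominator and no toxicity, one non-toxic early stop makes no difference to the conclusion, and two reverse it (100% against 80%). This assumes that neonates who stop early stay in the denominator. If they are replaced, the rate is inflated by a different route (for example 83% becoming 100%).

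How often early stops will occur cannot be judged from the document, so the probabilities above are illustrations, not forecasts. A reader might also infer that shorter exposure lowers the chance of toxicity and so favours the device further. That is plausible, but no figure in the protocol supports it.

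**What to change.** Use one definition, that of Study Objectives and Outcomes, in the Abstract, Sample Size and Statistical Analysis sections. Suggested content:

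- **Primary endpoint:** among included neonates who began BUBOLight PT, the proportion who received the full 4 hours of delivered illumination (brief pauses as described under Intervention allowed) and had no unacceptable and unexpected toxicity arising after PT began. The last clause is needed because Table 1 also ticks the safety items at hour 0.
- **Incomplete sessions:** counted as not a success, kept in the denominator and not replaced there.
- **Components:** report the completion rate and the toxicity-free rate separately.
- **Never started:** report separately the number included in whom PT did not begin. The Sample Size section refers to neonates included, and leaving these out without saying so could raise the rate.
- **Optional tidy-up:** in Variables and Data Collection, describe bilirubin as serving the secondary outcomes.

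The cost is wording only, since data on discontinuation and its causes are already to be collected. The reported primary rate may be less favourable than the toxicity-free rate alone.

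### The only post-baseline EDIN score is set at four hours of actual phototherapy, so a neonate stopped for good before then has none, and the 4-hour and change summaries cover completers only

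*Protocol article*

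**What the plan says.** Table 1 (Study Objectives and Outcomes) has five time columns: the start of phototherapy (H0), one hour, two hours, "4-hour effective phototherapy", and two hours after the end. The row "Evolution of the EDIN^a^ score: neonatal pain and discomfort scale" is ticked in two of them, H0 and the fourth. No column stands for an early stop.

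Statistical Analysis uses the same two times: "changes in the EDIN score between PT initiation (H0) and after 4 hours of actual treatment will also be described". It also says that "bilirubin levels and EDIN score data for neonatal pain and discomfort will be expressed as means, medians, quartiles, and minimum and maximum values at each" of these times, and that all data will be described individually.

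The Intervention section mentions EDIN without giving a time: the score is named in the same sentence as "the opinion of parents and health professionals on the use of the device will also be sought". Variables and Data Collection gives the range as 0-15 and adds no assessment.

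Incomplete sessions are not ruled out. Study Objectives and Outcomes lists causes of discontinuation among the key secondary objectives. Table 1 has a row "Number of feedings, number of diaper changes and the causes of cessation of phototherapy". Variables and Data Collection says that "data regarding PT discontinuation will be collected (including the number of changes, feedings, and cares").

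**The concern.** The second EDIN time exists only for a neonate who accumulates four hours of treatment. One taken off the device for good after, say, 90 minutes or three hours has an H0 score and nothing to compare it with. The change score is then a summary of those who got through the session.

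EDIN is the plan's scored measure of the neonate's pain and discomfort, and Statistical Analysis says that safety and acceptability will be judged from descriptive data. If the neonates who stop are those who tolerate the device less well, the missing scores are the high ones and the summary looks more comfortable than the experience was. With about ten neonates, one or two absent values can move the mean and the maximum. A score not taken at the bedside cannot be recovered at analysis.

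**Working it through.** **1. Is EDIN alone in this?** Follow-up times in Table 1, row by row, for a neonate stopped for good before four effective hours:

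| Row | Follow-up ticks | Any reachable after a stop? |
|---|---|---|
| Temperature, saturation, heart rate, contact reaction | 1 h, 2 h, 4 effective h | Yes, if still treated at 1 h or 2 h; heart rate and saturation are also recorded continuously |
| Adverse events | 1 h, 2 h, 4 effective h | Yes, likewise |
| Serum and transcutaneous bilirubin | 2 h after the end | Yes |
| Feedings, diaper changes, causes of cessation | 2 h, 4 effective h | Yes, at 2 h |
| Parents' perceptions | 2 h after the end | Yes |
| EDIN | 4 effective h | No |

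EDIN is the only row whose sole follow-up time requires completion. Statistical Analysis repeats that time, so two places agree on it.

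**2. The plan's own figure.** Sample Size sets a target of 9 of 10: 9/10 = 0.90, which reproduces. No power or precision figure can be checked, because the section says that the number was not calculated. The same section gives 10-15 neonates included for 10 evaluable pairs.

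**3. Share of treated neonates without a second score**, with k stops among N treated, is k/N:
- 1/10 = 10%. This is the shortfall that the target tolerates, if that one failure is an early stop.
- 2/10 = 20%.
- 5/15 = 33%. This is an upper bound: it assumes that 15 are treated and that all five non-evaluable neonates are early stops.

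**4. Effect on the mean change.** Let completers change by c on average and stoppers by d at the stop. The plan reports c. The all-treated mean is ((N − k)c + kd)/N, so the understatement is (k/N)(d − c). The documents give neither c nor d. Assume c = 0 and d = +3, +6 or +9:

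| Stops | d = +3 | d = +6 | d = +9 |
|---|---|---|---|
| 1 of 10 | 0.3 | 0.6 | 0.9 |
| 2 of 10 | 0.6 | 1.2 | 1.8 |
| 5 of 15 | 1.0 | 2.0 | 3.0 |

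For example, 5 × 6/15 = 2.0. On a 0-15 scale, a rise of 9 needs an H0 score of 6 or less. If d = c, meaning that stops have nothing to do with discomfort, the understatement is zero.

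**5. How likely is at least one missing score?** With early-stop risk r (assumed) and independent neonates, the chance is 1 − (1 − r)^N:
- r = 5%: 40% with 10 treated, 54% with 15.
- r = 10%: 65% and 79%.
- r = 20%: 89% and 96%.

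**The case against.** The strongest reply is that this is a condensed article. Its two statements agree, a change score at a fixed time is an ordinary definition, and assessments at withdrawal are often left to the full protocol or the case report form. This carries some weight: those documents may add a score at a stop. But the article does not leave the time open. It fixes it in the schedule and again in the analysis text, and anyone following either has no second score for a stopped neonate.

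A second reply is that the discontinuation wording may mainly mean short pauses, since it sits beside feedings and diaper changes, and the Intervention section uses it for a few minutes' break. That is fair. The protocol nowhere names discomfort as a reason for a permanent stop, so a link between stopping and discomfort is inference.

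Three stronger readings are tempting and are not supported:
- **That EDIN is the only objective measure of tolerance.** The documents do not call it objective. Vital signs, adverse events, and the comfort perceptions of parents and staff are also collected.
- **That the cause of a stop before two hours goes unrecorded.** The objectives and Variables and Data Collection gather discontinuation data without a time limit, and the 2-hour and 4-hour ticks can be read as tally points.
- **That poorly tolerated sessions vanish from the results.** Data are described individually, so a stopper appears with an H0 score, no second score and a recorded cause. Study Objectives and Outcomes bases the primary proportion on complete sessions, so on that wording a stop counts against the device.

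What remains after these replies is the missing score itself.

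**Conclusion.** The point holds in limited form. As scheduled, the 4-hour EDIN score and the change from H0 describe completers only; the H0 summary can still include everyone. The direction of any bias depends on stops being related to poor tolerance, and its size depends on assumed scores: 0.3 to 0.9 points on the mean with one stop in ten, and 1.0 to 3.0 in the upper-bound case of five in fifteen. If no session is stopped early, nothing is lost.

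EDIN is a descriptive secondary outcome in an uncontrolled pilot, with no test or threshold attached, and the primary endpoint does not use it. This is a worthwhile improvement and not a threat to the study's main conclusion.

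**What to change.** In Table 1 and in Statistical Analysis, define the second EDIN score as taken at the end of BUBOLight exposure: at four hours of actual treatment, or at an earlier permanent stop. Then:
- list the exposure time beside each score and flag early stoppers;
- state how many treated neonates contribute to the change;
- show the summary for 4-hour completers alongside the end-of-exposure summary.

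The cost is one bedside score for each stopped neonate and two changes of wording. Sample size, treatment and the decision to stop are untouched. The downside is that end-of-exposure scores come from differing exposure times, which is why the time must be listed and the completers' summary kept.
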